# Evaluation of the online-based self-help programme “Selfapy” in patients with unipolar depression: study protocol for a randomized, blinded parallel group dismantling study

**DOI:** 10.1186/s13063-021-05218-4

**Published:** 2021-04-09

**Keywords:** Major depressive disorders, Internet-based intervention, Blended treatment, Specialized mental healthcare, Routine practice, Randomized controlled trial

## Abstract

**Background:**

Patients with mild to moderate depressive symptoms can have limited access to regular treatment; to ensure appropriate care, low-threshold treatment is needed. Effective online interventions could increase the supply of low-threshold treatment. Further research is needed to evaluate the effectiveness of online interventions. This study aims to evaluate the online-based self-help programme “Selfapy” on a sample of depressive subjects and compares the impact of the programme’s unaccompanied version with its therapeutic accompanied version.

**Methods:**

A sample of 400 subjects that have a mild to severe depressive episode (Becks Depression Inventory - II and Hamilton Depression Scale) will be used. Subjects are randomly assigned to immediate access to an unaccompanied course (no support from psychologist via weekly phone calls), immediate access to an accompanied course (support from a psychologist via weekly phone calls) or a waiting list control group (access to the intervention after 24 weeks). The intervention will last for a period of 12 weeks. Depressive symptoms as a primary parameter, as well as various secondary parameters, such as life satisfaction, therapeutic relationships, social activation, self-esteem, attitudes towards Internet interventions and drop-out rates, are recorded at four different points in time: at baseline (T1), 6 weeks after the start of the intervention (T2), 12 weeks after the start of the intervention (T3) and 3 months after completion of the treatment follow-up (T4).

**Conclusion:**

This randomized and controlled, blinded study will make use of a “dismantled” approach to adequately compare the accompanied and unaccompanied versions of the intervention. Positive and meaningful results are expected that could influence the acceptance and implementation of online interventions.

**Trial registration:**

German Clinical Trials Register DRKS00017191. Registered on 14 June 2019

## Background

Depression is a common and severely distressing condition with a high mortality rate due to suicide and other factors [1, 2]. Depressive disorders are one of the largest global burdens with around 350 million people worldwide, while mild to moderate forms (29% of primary care patients) occur even more frequently than severe depressions (only 9.5% of primary care patients) [3, 4]. Subclinical depression refers to those who do not fully meet the criteria of a depressive episode (ICD-10) or major depression (DSM-5) [5] and is associated with considerable impairment, economic costs and increased risk for developing major depression [4, 6, 7].

Different treatment methods (e.g. cognitive behaviour therapy or pharmacotherapy) were shown to be effective in the treatment of depression [8]. Patients with mild to moderate depressive symptoms do not meet the requirements for currently available options of effective treatment [9, 10]. As there are too few options with low-threshold access, these patients do not receive treatment. There are few randomized controlled trials (RCTs) for low-threshold Internet interventions for those who have mild to moderate depressive symptoms. Low-threshold psychosocial interventions, including online self-help programmes, can be used as a complementary treatment, especially in the case of mild depression [11]. In general, over 20 RCTs, several meta-analyses and systematic reviews in the past have proven their effectiveness in the reduction of depressive symptoms compared to different control conditions (e.g. [12]). Drop-out rates in web-based interventions are typically high, especially in self-guided web-based interventions [13].

Cognitive behaviour therapy (CBT) is ideal for the implementation of online interventions due to its highly structured, directive and standardized nature, as well as its focus on psychoeducation and homework [9]. A systematic review and meta-analysis including 8 randomized studies with regard to Internet-delivered cognitive behaviour therapy (iCBT) was carried out by Zhou et al. [14]. Compared to the inactive control groups, the iCBT programmes were significantly more effective (SMD = − 0.28, CI [− 0.42, − 0.14]; *I*^2^ = 49%) in reducing depressive symptoms.

There are already a few online interventions for depression, but more high-quality trials are needed to prove efficacy [9–11, 15]. Online programmes are offered with or without therapeutic support. Therapeutic support can be delivered with the accompaniment of a clinical psychologist (accompanied) or in combination with conventional face-to-face therapy (blended). Unaccompanied programmes show small effect sizes in the treatment of depressive symptoms compared to the control group [16]. Unlike unaccompanied self-help programmes, accompanied self-help approaches involve regular contact with a clinical psychologist [17]. Accompanied self-help approaches also differ with respect to the intensity of therapeutic contact [15]. Accompanied online depression interventions show medium to large effect sizes compared to the control group [18, 19]. Meta-analyses provide some evidence that programmes that combine elements of traditional face-to-face therapy with an online programme are more effective than unaccompanied online programmes [18, 20]. Further research is necessary to draw conclusions regarding the differences in efficacy and impact between an accompanied and an unaccompanied online self-help programme.

The aim of this study is to validate the effectiveness of the online self-help programme “Selfapy” in an RCT. “Selfapy” offers the possibility of comparing an accompanied and unaccompanied version within the same programme. A randomized, controlled parallel-group study will be performed, and the differences between accompanied and unaccompanied versions of the courses, as well as their effects on treatment outcomes, will be evaluated.

### Trial objectives

With this trial, we evaluate the efficacy of the online self-help programme “Selfapy” and deduced the following hypotheses. The framework of the trial is superiority. The Becks Depression Inventory - II (BDI-II) [21] thereby serves as the primary outcome measure and assesses the depressive symptomatology.

#### Main hypotheses

Depressive symptoms (BDI-II scores) will be significantly lower in both study groups following the 3-month “Selfapy” programme compared to the control group.We expect higher depressive symptoms (BDI-II scores) in the unaccompanied group compared to the accompanied group.

#### Secondary hypotheses

The drop-out rate is expected to be higher for the unaccompanied group than for the accompanied group.The strength of the therapeutic relationship will be significantly higher in the accompanied group than in the unaccompanied group.Positive attitudes towards Internet interventions will increase for the accompanied group as well as for the unaccompanied group when compared with reported attitudes at baseline. Increased scores in positive attitudes towards Internet interventions will be significantly higher for the accompanied group than for the unaccompanied group.Quality of life, social activation and self-esteem scores will increase significantly over the duration of the 3-month programme compared to scores taken at baseline and compared to scores in the control group. The increase in these parameters will be significantly higher for the accompanied group than for the unaccompanied group.

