### Randomization and blinding

Subjects who meet the inclusion criteria will be randomly allocated to one of the three groups: (a) immediate access to the unaccompanied depression course of “Selfapy”, (b) immediate access to the accompanied depression course of “Selfapy” or (c) access to “Selfapy” after a delay of 24 weeks (control group).

Block randomization is performed by an independent researcher using a random number assignment plan for this list, which was created by a computer-controlled random number generator. These numbers are assigned blindly, i.e. subjects and researchers have no knowledge of which group a patient was allocated to. The subjects are randomly assigned to one of the three groups in a ratio of 2:2:1. The subjects will be informed by email about the result of the allocation process. Subjects in one of the intervention groups received an email with a link and their respective access code to register and be able to start the intervention immediately. Subjects in the control group who also received an email with a link that leads the subject to the assessment material will be informed by email about the result of the random assignment. Therefore, participants enrolled themselves in the study programme. Diagnostic interviewers are blind to the assigned group of subjects. An illustration of the patient flow can be found in Fig. 1.

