### Responses to crises and suicidality

A physical overuse can be excluded. The online survey at the time of measurement T1, T3 and T4 of the survey will take about 60 min (Table 2). The processing time for T2 is about 30 min. A general side effect of the interventions could possibly be a lack of treatment success. The most severe adverse event that could happen is acute suicidality. Suicidality is monitored using the BDI-II (after 6, 12 and 24 weeks) and the HRSD-24 (after 12 and 24 weeks). In case of a score of 3 (suicidal thoughts or behaviour) on item 3 on the HRSD-24 or in case of a score of 2 (suicidal thoughts or wishes) on item 9 of the BDI-II, discontinuation will be initiated. Each rater has an emergency plan, and the respective participant will be shifted to inpatient or outpatient psychotherapy.

**Table 2 Tab2:** Assessment tools utilized throughout the programme

Assessment timeframe	Assessment instrument
Pre (T1)	Self-assessment—questionnaires: BDI-II; QIDS-SR16; BAI; WHOQOL-BREF; SWOP-K9; WAI-SR; APOI; SASS; Bado
	Assessment by a therapist – Questionnaires: MINI; HRSD-24
During (T2)	Self-assessment—questionnaires: BDI-II; QIDS-SR16; BAI; WAI-SR; APOI
Post (T3)	Self-assessment—questionnaires: BDI-II; QIDS-SR16; BAI; WHOQOL-BREF; SWOP-K9; WAI-SR; APOI; SASS; Bado Assessment by a therapist—questionnaire: HRSD-24
Follow-up (T4)	Self-assessment—questionnaires: BDI-II; QIDS-SR16; WHOQOL-BREF; Bado Assessment by a therapist—questionnaire: HRSD-24

*Abbreviations*: *MINI*, Mini International Neuropsychiatric Interview; *BDI-II*, Beck Depression Inventory-II; *QIDS-SR16*, Quick Inventory of Depressive Symptomatology; *BAI*, Beck Anxiety Inventory; *WHOQOL-BREF*, WHO Quality of Life-BREF; *SWOP-K9*, Self-Efficacy, Optimism, and Pessimism Scale; *WAI-SR*, Working Alliance Inventory - Short Revised; *APOI*, Attitudes towards Psychological Online Interventions Questionnaire; *Bado*, basic documentation; *HRSD-24*, Hamilton Depression Scale; *SASS*, Social Activity Self-Assessment Scale

Subjects are allowed to attend ongoing psychotherapy. This reflects everyday treatment and ensures high external validity. Furthermore, it limits potential negative consequences due to the lack of treatment success, as additional treatment can be accessed, when needed. All potentially relevant factors for treatment outcome are taken into account for the statistical evaluation.

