#### Secondary outcome measures

Changes in depressive symptoms will be additionally assessed at baseline (T1) and post (T3) after 12 weeks as well as at follow-up (T4) using observer-rated inventories HRSD-24 and the QIDS [25].

Furthermore, changes in the self-assessment of anxiety-related symptoms will be analysed using the BAI [26]. Changes in self-esteem will be evaluated using the SWOP-K9 [27]. Similarly, the SASS [28] questionnaire will be utilized to record the levels of social activation. The WHOQOL-BREF [29] will be used to assess the impact of the programme on physical changes and life satisfaction. The APOI captures attitudes towards online interventions [30].

The WAI [31] is an employment inventory for the collection of therapeutic alliances and is used to evaluate work alliances. The ACSA is a self-anchoring rating scale for subjective well-being that was originally developed as a simple method to measure the quality of life consecutively in the patient-physician relationship [32]. The Bado sheet is used to assess the impact of the programme on subjects’ use of the healthcare system, including contact with healthcare providers, the number of therapy sessions and the amount of contact with psychotherapists and psychiatrists.

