### Planned statistical analysis

The recorded data of the different measurement times (T1, T2, T3 and T4) for both intervention groups and the control group are analysed. The treatment results of all subjects (pre-post difference) are analysed using intention-to-treat (ITT) analyses.

The primary endpoint is the decrease in depressive symptoms in the BDI-II (Delta BDI-II) between study entrance (T1) and the end of the intervention (T3). A one-way ANOVA (within factor “group”) is performed to analyse the differences in the decrease of depressive symptoms between the intervention groups. A Bonferroni correction for multiple testing is applied to examine the expected group differences. This correction is carried out using the formula *α*/*n* (with alpha level *α* = 0.05 and *n* = number of tests) in order to lower the level of significance, make fewer results significant and thus the number of false-positive results reduce.

In an exploratory analysis, the basic effectiveness of the intervention compared to the control condition is examined (accompanied and unaccompanied group vs. control group) in order to counter the high drop-out rate.

In addition, the mean values including confidence intervals (95%) are recorded. The data are aggregated in the form of mean values and standard deviations. No interim analyses are planned.

To check the data obtained from the measuring instruments for normal distribution, the Kolmogorov-Smirnov test is calculated at the beginning. For this purpose, the mean values and standard deviations of each variable, as well as the Kolmogorov-Smirnov *Z*-value, are calculated, and the asymptotic significance (two-sided) is determined. Values below 0.05 indicate a violation of the normal distribution.

The intermediate measurements are analysed with regard to continuous outcome measures using repeated-measure ANOVAs. Independent *t* tests and *χ*^2^ tests are used to estimate the intergroup differences in sample characteristics prior to treatment.

Missing values in the data are replaced by multiple imputations, as well as “last-observation-carried-forward” (LOCF), “baseline-observation-carried-forward” (BOCF) and a “reference-based multiple imputation” method (“jump-to-reference” approach) to replace the missing values.

Effect size calculations to measure the therapeutic success (before and after the intervention) are carried out by dividing the difference between the respective group mean values by their pooled standard deviation.

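### The first half of the attitudes hypothesis compares each programme arm only with its own baseline, without the randomised control arm (minor)

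*Protocol article*

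**What the plan says.** The Secondary hypotheses section of the protocol article states the attitudes hypothesis in two sentences. The first is "Positive attitudes towards Internet interventions will increase for the accompanied group as well as for the unaccompanied group when compared with reported attitudes at baseline"; the comparator is its closing phrase, "when compared with reported attitudes at baseline". The second is "Increased scores in positive attitudes towards Internet interventions will be significantly higher for the accompanied group than for the unaccompanied group". Neither mentions the control group.

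The next hypothesis in that section, on quality of life, social activation and self-esteem, refers change to both standards: "compared to scores taken at baseline and compared to scores in the control group". The first main hypothesis, on the BDI-II, is also stated against control.

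The instrument is named under Secondary outcome measures: "The APOI captures attitudes towards online interventions". Table 2 lists it at T1, T2 and T3 without separating the arms; the T2 row reads "BDI-II; QIDS-SR16; BAI; WAI-SR; APOI". Randomization and blinding speaks of "Subjects in the control group who also received an email with a link that leads the subject to the assessment material". Planned statistical analysis says that data from the four time points "for both intervention groups and the control group are analysed", but it describes no contrast for the APOI.

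**The concern.** A rise from an arm's own baseline mixes any effect of the programme with everything else that changes over twelve weeks, such as the passage of time and repeated completion of the same questionnaire. A randomised control arm exists to remove that mixture, and the protocol uses it for the neighbouring outcomes. It also states that the trial's framework is superiority, and a pre-post rise within an arm is not a superiority contrast.

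If the first sentence were followed as written, it could be declared confirmed even though control subjects had changed by the same amount. Attitudes are among the secondary parameters named in the abstract, and the authors expect the results to bear on acceptance of online programmes. A statement that the programme improves attitudes is therefore likely to be used.

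**Working it through.** **Comparators side by side (Main and Secondary hypotheses)**

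| Hypothesis | Own baseline | Control arm | Accompanied vs unaccompanied |
|---|---|---|---|
| BDI-II (main) | no | yes | yes |
| Attitudes, first sentence | yes | no | no |
| Attitudes, second sentence | no | no | yes |
| Quality of life, social activation, self-esteem | yes | yes | yes |

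An increase in attitudes under the programme is therefore judged only against baseline. The protocol gives no APOI figure, so there is nothing to reproduce. What follows is illustration.

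**Inputs.** From the Sample size section: 160 subjects per programme arm, 80 controls, 50% expected drop-out (leaving 80 and 40), alpha 0.05. Assumed: no programme effect, an upward drift shared by all arms of 0.10, 0.15 or 0.20 SD, a T1-T3 correlation r of 0.5, and a two-sided paired test.

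**Formula.** In SD units, SE of the mean change = sqrt(2(1 − r)/n). The chance of significance in a given arm is Φ(drift/SE − 1.96) + Φ(−drift/SE − 1.96).

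- n = 160: SE = sqrt(1/160) = 0.079. For 0.10 SD, drift/SE = 1.265, giving 0.244.
- n = 80: SE = sqrt(1/80) = 0.112. For 0.10 SD, drift/SE = 0.894, giving 0.145.

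| Shared drift | n = 160 | n = 80 |
|---|---|---|
| 0.10 SD | 0.244 | 0.145 |
| 0.15 SD | 0.475 | 0.269 |
| 0.20 SD | 0.716 | 0.432 |

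A noncentral-t calculation that counts significant increases only gives nearly the same: 0.241, 0.470 and 0.710 at n = 160; 0.141, 0.263 and 0.424 at n = 80. With no drift the figure is 0.025. With r = 0.7 the chances are higher: 0.368 to 0.901 at n = 160 and 0.206 to 0.626 at n = 80.

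The sentence claims a rise in both programme arms. If significance in both were required, the one-arm chances would be squared, because the arms are independent samples. At r = 0.5 that gives about 6% to 50% at n = 160 and 2% to 18% at n = 80, against 0.025² = 0.06% without drift.

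**With a control comparison.** Drift common to all arms cancels, and the error rate returns to 5% two-sided for each comparison (2.5% in favour of the programme). The price is power. At r = 0.5 the SD of change is 1, so for 160 vs 80 the SE is sqrt(1/160 + 1/80) = 0.137. Power is then 0.39 at d = 0.23 and 0.96 at d = 0.5. With 80 vs 40 it is 0.22 and 0.73. For a true change of 0.23 SD, the paired test would have 0.82 at n = 160 and 0.53 at n = 80. Adjusting for baseline recovers some power, since the residual variance is 1 − 0.5² = 0.75 instead of 1.

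**The case against.** Much of the case on the other side stands, and it limits the point.

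- **Half of the hypothesis is sound.** A reader might infer that the whole attitudes hypothesis is uncontrolled. It is not. The second sentence is a randomised contrast that serves the dismantling aim, and shared drift cancels in it. It still cannot show that either version raises attitudes beyond no programme.
- **No paired test is specified.** The first sentence says that attitudes will increase, without the word significantly, and the analysis section names no within-arm test for the APOI. The method for one secondary scale may be left to an analysis plan. The comparator, however, is stated here, and an analysis plan would have to follow it or depart from it.
- **Control APOI data are inferred.** A reader might take Table 2 as proof that controls complete the APOI. The same rows list the WAI-SR, a therapeutic-alliance measure, at T1 to T3 for all arms, although controls receive no treatment or support from the researchers. The table is evidently condensed. With the assessment link and the general statement on control data, collection is probable but not stated.
- **Drift may be absent or run the other way.** Regression to the mean is a weak argument here: entry depends on the BDI-II and the diagnosis, not on the APOI. Recruitment partly through the programme's own website may select favourable attitudes, which would then tend to fall.
- **The control contrast is not free of bias.** Control subjects learn their allocation by email and wait for access, and this may itself change their attitudes. The 5% error rate holds only for drift common to all arms.

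**Conclusion.** The point holds in a limited form. For the claim that attitudes rise in each programme arm, the protocol fixes the arm's own baseline as the only comparator, although it uses the control arm for the main hypothesis and for the neighbouring secondary one. Read as written, it could confirm a rise that controls share.

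The 24% to 72% (160 per arm) and 15% to 43% (80 per arm) are chances for a single arm. They rest on an assumed upward drift of 0.10 to 0.20 SD, a correlation of 0.5 and a paired test, none of which the protocol gives. They show how sensitive such a comparison is and do not estimate this trial's error rate. Nor does the protocol support the inference that a rise will be attributed to Selfapy: the sentence describes a change and states no cause.

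This is a minor point on one half of one secondary hypothesis. The primary BDI-II comparison and the other secondary outcomes are not affected.

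**What to change.** Add to the attitudes hypothesis a comparison of each programme arm with the control arm on the APOI at T3, adjusted for baseline APOI. Keep the accompanied against unaccompanied contrast, preferably in the same model, and label change from baseline within an arm as descriptive. State in Table 2 or the text that control subjects complete the APOI, if they do.

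If they do, the change costs one or two sentences and no new data. The downsides are lower power than a paired test, as shown above, and a control group whose attitudes may react to being on a waiting list; the second should be named as a limitation. If controls do not complete the APOI, the first half of the hypothesis should be kept as description only.

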## Methods

### Recruitment

A total of 400 subjects with mild to severe depressive symptoms are recruited via the “Selfapy” website, advertising on German television and in numerous information brochures from health insurance companies. The central recruiting tool is a study website (www.selfapy.de/studie/), where interested people can register to participate. If a person decides to participate by giving their consent, they will be immediately directed towards the determination of the deadline for the incoming survey (Mini International Neuropsychiatric Interview (MINI) [22], Hamilton Depression Scale (HRSD-24) [23]). Electronic informed consent has been recognized by previous ethics committees as a safe and ethical means of giving consent [24] and is used in this study. Additional consent would be required for the use of patient data in additional or supplementary studies.

